***c) Sampling***

Children admitted with severe malnutrition, defined by anthropometry according to WHO guidelines, will be recruited at CPGH, Mombasa, Kilifi County Hospital and Queen Elizabeth Central Hospital (QECH), Blantyre, Malawi.

*Sample size calculation*

Based on clinical data from the actual sites, we have observed that around 50% of patients to have transitioned to the second phase of treatment by day 5. We aim for a 10% absolute increase in percentage transitioned at day 5 to 60%, which gives a hazard ratio of 1.35. Sample size for survival time was calculated using the *stpower* command in Stata version 12. Using α=0.05, 80% power, the number of patients required to demonstrate a hazard ratio of 1.35 is 381 per arm. We will aim at 420 per arm to allow for contingencies. It is anticipated that 400 children will be enrolled at CPGH, 120 at KCH and 320 at QECH. However, these figures will be adjusted in line with actual recruitment.

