|  | % Energy | | Quantity: g/1000ml | |
| --- | --- | --- | --- | --- |
|  | **Standard F75** | **Modified F75** | **Standard F75** | **Modified F75** |
| Protein | 5.3% | 5.3% | 9.9 | 9.9 |
| Lipid | 31.5% | 51.7% | 26.3 | 43.1 |
| Carbohydrate | 63.2% | 43.0% | 118.5 | 80.6 |
| **Total** | **100%** | **100%** | **154.7** | **133.6** |
|  |  |  |  |  |
| Lactose | 9.9% | 0% | 18.6 | 0 |
| Sucrose | 3.6% | 3.6% | 6.8 | 6.8 |
| Maltodextrin | 50% | 39% | 93.2 | 73.9 |

*Formulations of standard F75 and modified F75*

*Randomisation*

Sequential study numbers will be generated for each site according to a prepared blocked randomisation list of random block sizes before the study begins. Randomisation codes linking allocation to study number will be held by the local safety monitor and chair of the DSMC be opened only in case an individual safety concern or until the database is unlocked. Children will be allocated study numbers sequentially within each site, thus randomly allocating the intervention and maintaining blinding. Group allocation will remain unknown to participants and trial personnel, including the trial-coordinator and principal investigator. Code breaks will be provided to the research team, to be used only in the case of an emergency; 24 hour access will be provided to these code breaks by mobile phone.

*Clinical care*

Children will be managed to the best standard available in each facility, in line with the Kenyan and WHO recommendations. HIV testing by rapid antibody test is routinely offered by the hospitals involved in the trial at admission to all severely malnourished children through ‘provider initiated testing’ according to the current National Guidelines for HIV Testing and Counselling in Kenya (2008) and appropriate follow up tests and referral for care are undertaken according to the results.

*Follow up*

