Children will be examined daily whilst in hospital and clinical status recorded on a standardised proforma (appendix d). A blood sample and stool sample will be taken at day 3 to assess for metabolic effects of refeeding and carbohydrate malabsorption. If children deteriorate during the transition phase or phase 2 and are placed back on phase 1, they will receive the same F75 intervention diet as allocated during the initial treatment. The decision to discharge will be made by the usual clinical team rather than trial personnel. Food supplements and/or nutritional counselling and follow up in the nutritional clinic that are the current standard of care at each institution will also be done at discharge. No study follow up after discharge will be done.

[figure not shown]

*Outcome measures*

*Primary outcome:* the choice of primary outcome is based on the therapeutic purpose of F75, which is to achieve stabilisation and thereby allow a child to progress to feeds with higher protein and energy content to enable catch-up growth.

The primary outcome is stabilisation, defined as having reached the second (transition) phase of treatment. The criteria for stabilisation will be according to WHO guidelines:

Absence of any WHO danger or emergency signs: obstructed breathing, respiratory distress, cyanosis, shock (delayed capillary refill plus fast & weak pulse plus temperature gradient), severe anaemia (Hb<5g/dl), congestive cardiac failure, impaired consciousness, convulsions, severe dehydration, profuse watery diarrhoea, vomits everything, hypothermia.

*and*

If there is oedema at baseline, loss of oedema defined as improving from a severe +++ oedema (severe: generalized bilateral pitting oedema including feet, legs, arms and face) to ++ oedema (moderate: no upper arm or upper leg oedema and no facial oedema or from ++ oedema to + (mild: only feet/ankle oedema) or none;

*and*

Tolerating full prescribed volume of F75 feeds and observed to be completing the feeds.

For analysis, children who die before stabilisation will be classified as ‘not transitioned’.

*Pre-specified secondary outcomes*:

1. Number days with diarrhoea (3 or more loose stools within 24h);
2. Number days requiring rehydration fluids (ReSoMal or IV fluids);
3. Percentage change in weight between admission and day 5;
4. Changes in sodium, potassium, magnesium, calcium, phosphate and albumin between admission and day 3;
5. Faecal electrolytes, pH and fat at day 3;

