### ***Laboratory procedures***

Blood tests for clinical care such as full blood counts, electrolytes and liver function will be undertaken as usually done for clinical care at each site. In addition, a plasma sample will be stored at admission and day 3 in order to measure sodium, potassium, calcium, magnesium, phosphate and albumin by standard methods at the end of the study in Kilifi. Plasma samples from Kenya and Malawi will be analysed for evidence of gut dysfunction and permeability including IL-1b, IL-6, IL-8, IL-10, TNFα, IFNϒ, LPS, sCD14 and intestinal fatty acid binding protein by ELISA and multiplex bead array methods in Kilifi and/or at the Hospital for Sick Children, Toronto, Canada.

Stools will be homogenised by stirring and stored at minus 80 degrees C in sterile tubes in Kilifi. At the end of the trial, stored stools from admission and day 3 will be analysed. Stools will be analysed by multiplex PCR for diarrhoeal viral pathogens in Kilifi using our existing long-term surveillance platforms and by light microscopy following filtration and concentration processing for helminths and protozoa. These assays will be performed in Kilifi. Analyses will further consist of specialised tests: faecal electrolytes as a marker of osmotic vs. secretory diarrhoea, faecal fat, faecal pH as markers of carbohydrate malabsorption and calprotectin as a marker of intestinal inflammation and will be performed together with samples from Malawi in Kilifi and at the University of Groningen, the Netherlands. Analyses of the faecal bacterial microbiome using pyrosequencing and biomarkers of intestinal (dys)-function using mass spectrometry will be analysed in Kilifi and/or at the Hospital for Sick Children, Toronto, Canada. Since these techniques are not yet fully established in Kilifi, skills and technology will be transferred from Canada to the Netherlands to Kilifi, in order that these assays will be done locally with validation from the eternal laboratories. Remaining samples will be stored in Kilifi for up to 5 years future studies of pathophysiology, subject to approval by SSC and ERC.

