### (b) Data management/analysis

The trial will use the GCP-compliant Openclinica (<https://openclinica.com/> ) database system, which will be hosted at KWTRP in Kenya. Originally developed for small oncology trials, this system has become the leading open-source clinical data capture system for clinical trials. It allows secure remote data entry online from the sites, provides a real-time reporting system and flagging of inconsistencies and database changes for monitoring. We have used this system for several large clinical trials, which have been programed and maintained by the data manager who will be working on this trial. The trial will be register on clinicaltrials.gov along with pre-specified endpoints. Data cleaning and record verification will be completed and a written analysis plan agreed before the database is un-blinded.

Descriptive statistics on baseline characteristics of the participants in each arm will be provided. Bias will be determined by maintaining a screening log of all potentially eligible participants and those who were excluded or randomized into the two arms. This will be presented as a flow diagram in the final published report according to CONSORT statement guidelines.

The primary outcome will be assessed using a Kaplan-Meier analysis and Cox proportional hazards analysis comparing the rate of stabilisation between arms. Differences between arms in the number of days to stabilisation will be compared using a two tailed Mann-Whitney *U* test. Children who die prior to stabilisation will be included in the primary analysis as ‘not stabilised’. Secondary endpoints with binary outcomes (e.g. overall mortality) will be analysed using contingency tables and a chi squared test. Where adjustment for baseline parameters is required, relative risks will be calculated. For continuous variables and count data (e.g. days receiving rehydration fluids or days with diarrhoea), a suitable general linear model (e.g. linear regression, Poisson regression) will be used. For time to discharge, Kaplan-Meier and Cox proportional hazards analysis will be used. These analyses are conducted on the intention-to-treat principle and are considered the confirmatory analysis. We will conduct tests of heterogeneity of effect, and effect modification for both kwashiorkor and HIV infection, which are considered, *a priori,* to potentially alter the response to F75.

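### Outcome 4 (change in six plasma analytes to day 3): naming the admission value as a covariate would gain precision at no cost

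*Protocol*

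**What the plan says.** In section 8, d) Procedures, under the outcome measures, secondary outcome 4 reads "Changes in sodium, potassium, magnesium, calcium, phosphate and albumin between admission and day 3". The laboratory section confirms that both values will exist for each analyte: "a plasma sample will be stored at admission and day 3 in order to measure sodium, potassium, calcium, magnesium, phosphate and albumin".

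Section 9(b), Data management/analysis, says that for continuous variables and counts "a suitable general linear model (e.g. linear regression, Poisson regression) will be used". Covariates are neither listed nor excluded. Baseline adjustment appears once, directly after the binary outcomes: "Where adjustment for baseline parameters is required, relative risks will be calculated". On the status of the set, the section says "These analyses are conducted on the intention-to-treat principle and are considered the confirmatory analysis". It also promises "a written analysis plan agreed before the database is un-blinded". That plan is not at hand.

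**The concern.** The outcome is written as a difference between two values, and the only sentence on baseline adjustment concerns an effect measure for binary outcomes. The most literal analysis is therefore a linear model of change on arm alone. That model subtracts the whole admission value, which amounts to fixing the slope of day 3 on admission at 1. If the actual slope is below 1, the change score over-corrects. It then carries more variance than necessary, and a chance difference between arms at admission reappears in the result with the opposite sign.

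The stake is power on the biochemical outcomes. The introduction builds the refeeding rationale on phosphate, potassium, magnesium and sodium, and the day 3 blood sample is taken to look for metabolic effects of refeeding. The trial is sized only for time to stabilisation, so precision on these analytes depends on how they are analysed.

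**Working it through.** **Inputs.** The protocol gives no standard deviation, effect size, correlation or power for outcome 4, so there is no planned figure to reproduce. From the documents: the target size ("We will aim at 420 per arm to allow for contingencies", section 8, c) Sampling), equal numbers per arm, and alpha 0.05, which is stated for the primary outcome and taken here as two-sided. Assumed: equal SD at admission and day 3, correlation rho between them (shown over a range), and complete pairs in all 420 per arm, which is an upper bound.

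**Direction.** Write SD_b and SD_y for the admission and day 3 SDs.

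- Variance of change: SD_y² + SD_b² − 2·rho·SD_y·SD_b
- Variance after adjustment for admission: (1 − rho²)·SD_y²
- Difference: (SD_b − rho·SD_y)², which is never negative

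Apart from the one degree of freedom spent on the covariate, adjustment therefore cannot lose precision, even if the SDs differ. It gains nothing only when the slope rho·SD_y/SD_b equals 1.

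**Size, equal SDs (in units of SD²).** Change: 2(1 − rho). Adjusted: 1 − rho². Ratio adjusted/change: (1 + rho)/2. If change by arm has 80% power, adjusted power = Φ(2.802/√ratio − 1.960). If the adjusted analysis has 80% power, change-by-arm power = Φ(2.802·√ratio − 1.960).

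| rho | change | adjusted | ratio | variance cut | adjusted power when change has 80% | change power when adjusted has 80% |
|---|---|---|---|---|---|---|
| 0.3 | 1.40 | 0.91 | 0.65 | 35% | 0.935 | 0.617 |
| 0.5 | 1.00 | 0.75 | 0.75 | 25% | 0.899 | 0.679 |
| 0.7 | 0.60 | 0.51 | 0.85 | 15% | 0.860 | 0.733 |
| 0.9 | 0.20 | 0.19 | 0.95 | 5% | 0.820 | 0.780 |

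At rho 0.5 and 420 per arm, the difference detectable with 80% power is 2.802 × √(2/420) × √1.00 = 0.193 SD by change and 2.802 × √(2/420) × √0.75 = 0.167 SD after adjustment.

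**Chance imbalance.** Randomisation is blocked within site ("Sequential study numbers will be generated for each site according to a prepared blocked randomisation list of random block sizes"). That balances numbers, not analyte levels. The standard error of the arm difference at admission is √(2/420) = 0.069 SD, so its 95% range is about ±1.96 × 0.069 = ±0.135 SD. An imbalance of 0.1 SD shifts the change comparison by −(1 − rho) × 0.1 SD: −0.07, −0.05, −0.03 and −0.01 SD at rho 0.3, 0.5, 0.7 and 0.9.

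**Validity.** In 3,000 simulated trials with no effect, 420 per arm, at each of rho 0.3, 0.5 and 0.7, the mean arm difference in unadjusted change was essentially zero (−0.0013, −0.0009 and 0.0002 SD) and type I error was 0.050, 0.040 and 0.044. The change comparison is valid, only less precise.

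**Does the outcome need redefining?** No. Change equals the day 3 value minus the admission value. With the admission value in the model, that subtraction lowers the covariate's coefficient by 1 and leaves the arm coefficient untouched. In the simulation the two arm effects agreed to about 10⁻¹⁵.

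**The case against.** The strongest objection is that the protocol nowhere prescribes an unadjusted analysis. A linear model can carry the admission value, a change outcome is compatible with it, the model wording is openly illustrative, and a separate analysis plan is promised. Covariates for a secondary outcome are ordinary content for that plan. This stands. A reader might infer that the protocol fixes an analysis without baseline adjustment, but that would be reading a decision into silence. The loss arises only if the analysis plan also omits the covariate.

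A reader might also infer that chance imbalance biases the result. It does not: over repeated randomisation the change comparison is unbiased, and its confidence interval already reflects this variation. The point about imbalance is conditional on the one randomisation obtained.

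Finally, the size rests on an unknown rho and on complete pairs. Deaths and missed samples will reduce the 420, and at rho 0.9 the variance gain is only 5%. This too stands, and it is why a range is given. What remains is that the outcome is written as a change, the analyses are called confirmatory, and the one reference to baseline adjustment points elsewhere. Naming the covariate settles the matter before unblinding.

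**Conclusion.** The point holds as a free improvement, not as an error in the protocol. Read literally, outcome 4 leads to a comparison of change by arm that is valid but less precise than one adjusted for the admission value. Under equal SDs the excess variance factor is 2/(1 + rho): 1.54, 1.33, 1.18 and 1.05 at rho 0.3, 0.5, 0.7 and 0.9. The direction does not depend on the equal-SD assumption; the size does, and it depends on a correlation that the documents do not give. The documents do not support the stronger conclusions that adjustment has been ruled out, or that the planned comparison would be biased. The primary outcome and its sample size are not affected.

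**What to change.** Add one sentence to section 9(b), or to the analysis plan before unblinding: each plasma analyte in outcome 4 is compared between arms by linear regression with the admission value of the same analyte as a covariate, and the adjusted arm difference is reported with its 95% confidence interval.

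The definition of outcome 4 can remain, since adjusted change and adjusted day 3 value give the same arm difference. Mean change by arm can still be shown descriptively.

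The cost is that sentence. Both samples are already to be stored and assayed, and a child without an admission value has no change score anyway, so no data, blood or participants are added or lost.

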***Monitoring of adverse events***

This group of children are expected to have a high frequency of adverse events regardless of this intervention. There is no specific toxicity profile associated with F75 milk. The study team will monitor children through daily clinical examination. Laboratory tests including a full blood count, electrolytes, blood glucose and liver function tests will be done as guided by requirements for clinical care. Serious adverse events, include events that are life-threatening or prolong hospital admission are pre-specified as secondary endpoints number vi) and vii) above. These will be recorded and entered on the trial database. A summary of serious adverse events will be reported quarterly, and examined in an un-blinded analysis by the DSMB at the trial mid-point and again at the end of the trial.

***Monitoring of study procedures***

Study monitoring will be conducted to ensure that the conduct of the study complies with ICH Guidelines and the trial’s standard operating procedures. In Kenya, the trial will be monitored by the KEMRI/Wellcome Clinical Trials Facility Monitoring Team. A comprehensive study initiation visit will be done at which all staff will be trained in protocol specific procedure, and check that all trial logistics are in place. Routine monitoring will be conducted every three months or more frequently if required. The monitor’s role is part of the quality system that will ensure that the study file is maintained with updated master file documents, that all participants have dully completed informed consent and that staff on the study are following their SOP’s in accordance to protocol and applicable regulatory norms.

### ***Laboratory procedures***

Blood tests for clinical care such as full blood counts, electrolytes and liver function will be undertaken as usually done for clinical care at each site. In addition, a plasma sample will be stored at admission and day 3 in order to measure sodium, potassium, calcium, magnesium, phosphate and albumin by standard methods at the end of the study in Kilifi. Plasma samples from Kenya and Malawi will be analysed for evidence of gut dysfunction and permeability including IL-1b, IL-6, IL-8, IL-10, TNFα, IFNϒ, LPS, sCD14 and intestinal fatty acid binding protein by ELISA and multiplex bead array methods in Kilifi and/or at the Hospital for Sick Children, Toronto, Canada.

Stools will be homogenised by stirring and stored at minus 80 degrees C in sterile tubes in Kilifi. At the end of the trial, stored stools from admission and day 3 will be analysed. Stools will be analysed by multiplex PCR for diarrhoeal viral pathogens in Kilifi using our existing long-term surveillance platforms and by light microscopy following filtration and concentration processing for helminths and protozoa. These assays will be performed in Kilifi. Analyses will further consist of specialised tests: faecal electrolytes as a marker of osmotic vs. secretory diarrhoea, faecal fat, faecal pH as markers of carbohydrate malabsorption and calprotectin as a marker of intestinal inflammation and will be performed together with samples from Malawi in Kilifi and at the University of Groningen, the Netherlands. Analyses of the faecal bacterial microbiome using pyrosequencing and biomarkers of intestinal (dys)-function using mass spectrometry will be analysed in Kilifi and/or at the Hospital for Sick Children, Toronto, Canada. Since these techniques are not yet fully established in Kilifi, skills and technology will be transferred from Canada to the Netherlands to Kilifi, in order that these assays will be done locally with validation from the eternal laboratories. Remaining samples will be stored in Kilifi for up to 5 years future studies of pathophysiology, subject to approval by SSC and ERC.

## 9) Data

### (a) Data storage

The principal and site investigators will maintain appropriate medical and research records for this trial, in compliance with ICH E6 GCP and regulatory and institutional requirements for the protection of confidentiality of subjects. Permission may be granted for the examination, analysis, verification and reproduction of any records and reports that are important to evaluation of a clinical trial. Any party (e.g., domestic and foreign regulatory authorities, sponsor's monitors and auditors) with direct access should take all reasonable precautions within the constraints of the applicable regulatory requirement(s) to maintain the confidentiality of subjects' identities and sponsor’s proprietary information. All records will be kept in a locked filing cabinet, which is accessed only by the investigators and the study nurses. All computer entry and networking programs will be done with coded numbers and initials only.

### (b) Data management/analysis

The trial will use the GCP-compliant Openclinica (<https://openclinica.com/> ) database system, which will be hosted at KWTRP in Kenya. Originally developed for small oncology trials, this system has become the leading open-source clinical data capture system for clinical trials. It allows secure remote data entry online from the sites, provides a real-time reporting system and flagging of inconsistencies and database changes for monitoring. We have used this system for several large clinical trials, which have been programed and maintained by the data manager who will be working on this trial. The trial will be register on clinicaltrials.gov along with pre-specified endpoints. Data cleaning and record verification will be completed and a written analysis plan agreed before the database is un-blinded.

Descriptive statistics on baseline characteristics of the participants in each arm will be provided. Bias will be determined by maintaining a screening log of all potentially eligible participants and those who were excluded or randomized into the two arms. This will be presented as a flow diagram in the final published report according to CONSORT statement guidelines.

The primary outcome will be assessed using a Kaplan-Meier analysis and Cox proportional hazards analysis comparing the rate of stabilisation between arms. Differences between arms in the number of days to stabilisation will be compared using a two tailed Mann-Whitney *U* test. Children who die prior to stabilisation will be included in the primary analysis as ‘not stabilised’. Secondary endpoints with binary outcomes (e.g. overall mortality) will be analysed using contingency tables and a chi squared test. Where adjustment for baseline parameters is required, relative risks will be calculated. For continuous variables and count data (e.g. days receiving rehydration fluids or days with diarrhoea), a suitable general linear model (e.g. linear regression, Poisson regression) will be used. For time to discharge, Kaplan-Meier and Cox proportional hazards analysis will be used. These analyses are conducted on the intention-to-treat principle and are considered the confirmatory analysis. We will conduct tests of heterogeneity of effect, and effect modification for both kwashiorkor and HIV infection, which are considered, *a priori,* to potentially alter the response to F75.

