**4) Introduction**

Admission to hospital with complicated severe acute malnutrition (SAM) in Africa commonly has a case fatality of 10-30%.[^1-3^](#_ENREF_1) Importantly, children are usually admitted to hospital because they are severely ill rather than for malnutrition alone. Mortality may be improved to some extent by adherence to WHO recommended management,[^1^](#_ENREF_1)^,^[^2^](#_ENREF_2) but the direct application of these guidelines to all contexts is controversial.[^4^](#_ENREF_4) The WHO guidelines were designed on the basis of historical data on nutrient requirements and medical treatments and almost none of the recommendations are supported by evidence from clinical trials.

For the treatment of complicated inpatient SAM, the guidelines consist of three distinct phases of treatment:[^5^](#_ENREF_5) phase 1 or stabilization phase where a low protein, liquid diet (F75) is introduced with a reduced energy intake (80-100 kcal/kg/day). Once a child has stabilised, there is a ‘transition phase’ consisting of either ready to use therapeutic foods (RUTF) with supplemental F75 or alternatively another milk formula known as F100. RUTF is a peanut based, energy dense supplement used to obtain catch-up growth. F100 is a liquid formula with a higher energy density and protein content than F75. The caloric intake is increased daily to a maximum of 130 kcal/kg/day. Finally, ‘Phase 3’ is the recovery phase during which the aim is to achieve catch-up growth with either RUTF or F100.

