Typically, the highest mortality rate is found in the early phases of treatment. Children who fail treatment early often have profuse diarrhoea, signs of circulatory insufficiency which is hard to treat. The most recent reports from Zambia and Kenya note a prevalence of diarrhoea of more than 60% amongst children with SAM and it is associated with increased mortality.[^6^](#_ENREF_6)^,^[^7^](#_ENREF_7) Currently at Kilifi County Hospital and Coast Provincial General Hospital, ~20% of children are given either a diluted or lactose-free milk feed during rehabilitation of SAM (unpublished data), although there are no specific guidelines for this. Diarrhoea may be caused by a viral or bacterial gastroenteritis, sepsis, or may be nutritionally induced (osmotic). There are no routinely available tests to distinguish osmotic from infective or other causes of diarrhoea in hospitals in sub-Saharan Africa. Rotavirus vaccine will be introduced in 2014 and its contribution to diarrhoea amongst children with SAM is unknown.

The proportion of energy derived from carbohydrates in F75 is high. The carbohydrates in F75 milk (as well as F100 and RUTF) consist of a mixture of maltodextrin, sucrose and lactose. Disaccharides such as maltose, lactose or sucrose are normally hydrolysed into monosaccharides by disaccharidases localized at the tip of small intestinal villi. The monosaccharides such as glucose and galactose can then be transported across the apical membrane through Na^+^ dependent glucose transporter, whilst fructose makes use of a facilitative fructose transporter. There is limited information on the intestinal function and intestinal carbohydrate absorption in malnourished children. However, data from Jamaica and South Africa suggest that there is impaired absorption of disaccharides (lactose and sucrose), regardless of the presence or suspicion of gastroenteritis.[^8^](#_ENREF_8)^,^[^9^](#_ENREF_9) Limited histological evidence has shown intestinal atrophy in children with SAM.[^10-12^](#_ENREF_10) These data are consistent with clinical signs of lactose malabsorption found in children with severe malnutrition.[^13^](#_ENREF_13) Recently, evidence of impaired absorption of monosaccharide glucose in children with SAM was reported in Malawi.[^14^](#_ENREF_14)

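### The primary analysis gives children who die a status ('not stabilised') but no time at risk, and the two ways of coding them in Kaplan-Meier and Cox can give different primary conclusions

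*Protocol*

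**What the plan says.** The analysis method is in protocol section 9(b): "The primary outcome will be assessed using a Kaplan-Meier analysis and Cox proportional hazards analysis comparing the rate of stabilisation between arms". The same paragraph gives the rule for deaths, "Children who die prior to stabilisation will be included in the primary analysis as" 'not stabilised'. The outcome definition in section 8(d) agrees in substance: "For analysis, children who die before stabilisation will be classified as" 'not transitioned'.

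Neither place gives a time for these children, a fixed analysis horizon or a competing-risk method. Two neighbouring analyses are also open:
- "Differences between arms in the number of days to stabilisation will be compared using a two tailed Mann-Whitney" U test, with no value or rank for a child who dies and so has no number of days.
- "For time to discharge, Kaplan-Meier and Cox proportional hazards analysis will be used", with no rule for deaths at all.

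The section calls these analyses confirmatory. It also says that a written analysis plan will be agreed before unblinding; that plan is not at hand.

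**The concern.** A time-to-event analysis needs an event indicator and a time for each child, and the protocol supplies only the indicator. A programmer given 'no event' and no time rule will normally enter the last day observed, which is the day of death. The child then leaves the risk set and is treated as exchangeable with surviving children who have yet to stabilise. A child who has died cannot stabilise, so this defeats the evident aim of the rule.

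Death is not rare in this population. The introduction says that admission with complicated severe acute malnutrition "commonly has a case fatality of 10-30"%, and adds: "Typically, the highest mortality rate is found in the early phases of treatment". Early treatment is also when stabilisation is measured. If deaths are censored, a formula that raises early mortality need not lose on the primary outcome, and could look better if the children who die are those slowest to stabilise. The interim Haybittle-Peto guidance refers to the primary outcome as well as safety, so the same uncertainty enters a possible stopping recommendation.

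**Working it through.** **The plan's own figure.** Section 8(c) gives 381 per arm. Freedman's formula with two-sided alpha 0.05 (sidedness is not stated), 80% power and event-free proportions 0.5 and 0.6 gives:
- HR = ln 0.6 / ln 0.5 = 0.737 (inverse 1.357)
- events = 7.849 × (1.737/0.263)², rounded up to 343
- 343 / 0.45 = 762 in total, or 381 per arm

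The figure reproduces. It contains no explicit allowance for death as a competing event.

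**Inputs for the check.** From the protocol: 420 per arm; "around 50% of patients to have transitioned to the second phase of treatment by day 5"; HR 1.35. Assumed, because the protocol gives no figure: constant hazards, 30 days of follow-up, times in whole days, and 15% of control children dying before stabilisation. Hazards per day are λ = 0.151 (stabilisation) and μ = 0.027 (death).
- Control deaths: 0.027/0.178 = 15.2%.
- Control stabilised by day 5: λ/(λ+μ) × (1 − e^(−5(λ+μ))) = 0.848 × (1 − e^(−0.89)) = 0.50, as planned.

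**Case 1: death hazard doubled, stabilisation hazard unchanged.** Deaths in the modified arm are 0.054/0.205 = 26.3%.
- Censored at death, one minus Kaplan-Meier estimates 1 − e^(−λt). At day 10 that is 1 − e^(−1.51) = 78% in both arms.
- The true proportions stabilised by day 10 are 0.848 × (1 − e^(−1.78)) = 71% in control and 0.737 × (1 − e^(−2.05)) = 64% in the modified arm.
- Simulated Cox models: HR about 0.98 censored, with harm flagged in 3 to 4% of trials; HR about 0.81 with the dead kept at risk to day 30, with harm flagged in about 79 to 82%.

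**Case 2: stabilisation HR 1.35, death hazard doubled.** The modified-arm stabilisation hazard is 1.35 × 0.151 = 0.204, and deaths are 0.054/0.258 = 20.9%.
- Benefit is declared in about 93% of trials censored and about 3% kept.
- The true cumulative curves cross. By day 5 the proportions stabilised are 0.791 × (1 − e^(−1.289)) = 57% against 50%; by day 30 they are 79% against 84%. So the 3% means no overall advantage, not proof of harm, and the time to which deaths are carried must be stated.

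**Case 3: planned benefit (HR 1.35), death hazard unchanged.** Power is about 97% censored and 81% kept at 15% control deaths, and about 87% kept at 10%.

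**Sensitivity, continuous times, no effect on stabilisation (200 runs per scenario):**

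| Deaths, control vs modified | HR censored | HR kept |
|---|---|---|
| 10% vs 20% | 1.00 | 0.82 |
| 10% vs 30% | 1.00 | 0.67 |
| 16% vs 23%, sickest children die | 1.11 | 0.89 |
| 16% vs 27%, sickest children die | 1.19 | 0.82 |

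The last two rows assume that 30% of children both stabilise slowly and die more often. The arm with more deaths then looks better when deaths are censored.

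**Would the mortality test see it?** Counting only the deaths above, 420 per arm:
- Case 1: difference 0.112, standard error √((0.152×0.848 + 0.263×0.737)/420) = 0.0277, z = 4.0, power about 98%.
- Case 2: difference 0.058, standard error 0.0265, z = 2.2, power about 60%.

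**The case against.** A reader might infer that the protocol censors deaths. It does not say so. Including these children as 'not stabilised' can equally mean keeping them in the denominator as failures, which does penalise death. What stands is that the text does not choose between the readings.

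A reader might also infer that a harmful formula would pass unnoticed. The documents do not support that. Mortality until discharge is a pre-specified secondary outcome with its own chi-squared test among the confirmatory analyses. Serious adverse events are also reviewed unblinded at mid-point and at the end. In case 1 the mortality test does better than the repaired primary analysis. In case 2, however, it misses about 40% of trials while the censored primary analysis nearly always reports benefit.

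Third, the 10-30% is overall case fatality. The share dying before stabilisation is not given, and with few such deaths the two codings would nearly agree.

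Fourth, the null hypothesis concerns the rate of stabilisation, and a cause-specific hazard ratio read with mortality is a recognised analysis of a rate. That is fair, but censoring at death would not carry out the protocol's own rule that a death counts as not stabilised.

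Finally, such detail often sits in the analysis plan, which may settle it. But here the protocol itself fixes both the method and a rule for deaths, and together they are incomplete. Time to discharge is a secondary matter.

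**Conclusion.** The point holds as an incomplete rule on the confirmatory primary analysis, and should be fixed. The protocol gives deaths a status without a time; the default coding in the named methods censors them; and the alternative treats them as failures. Under the stated assumptions the choice moves the hazard ratio from about 0.98 to 0.81 when only deaths increase. It moves the chance of declaring benefit from about 93% to 3% when faster stabilisation comes with a doubled death hazard. The direction is stable across the death rates tried; the size depends on the assumed pre-stabilisation deaths, the 30-day horizon and constant hazards. The defect is a primary result that can mislead when read alone. It is not a stated decision to censor deaths, and not a trial blind to mortality.

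**What to change.** In section 9(b), and in any analysis plan before unblinding:
- State that children who die before stabilisation remain in the risk set as never stabilised to a fixed common time, and name that time (a subdistribution-type hazard ratio).
- Replace one minus Kaplan-Meier with the cumulative incidence of stabilisation.
- Report the cause-specific hazard ratios for stabilisation and for death beside the primary estimate.
- Give deaths the worst rank in the Mann-Whitney test.
- Apply the same rule to time to discharge.

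The cost is a few sentences and no new data. The downside is lower power than with censoring: about 81% against 97% at 15% control deaths, and about 87% at 10%. That is still about the stated 80%. Power falls as the death share rises, so it should be rechecked if pre-stabilisation mortality is expected above 15%.
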